#### Sample size estimation

We aim to recruit 500 participants. A sample of 294 (half from NHS and half from independent sector units) will allow us to detect a mean difference in inpatient days of 0.38 SD (REAL study SD = 113, i.e. around 6 weeks) [7] between NHS and independent sector rehabilitation units, using a two-sample t test with 90% power and 5% significance level. Based on a bed day cost of £350, 6 weeks is an important difference, representing a potential saving of £14,700 per patient.

To perform the multivariable regression analysis described below, this sample size is increased to 350 after inflating, using a variance inflation factor (VIF) of 1.19 (derived using a multiple correlation coefficient of 0.16, the assumed proportion of variance in the service type explained by its association with the confounding variables). We do not have estimates available for the VIF from previous studies and thus assumed a moderate strength of association between service sector and the confounding variables [34]. The sample size further increases to 497 after allowing for a design effect (DE) of 1.42 (based on an average cluster size of 8 and an intracluster correlation of 0.06) [4].

Based on the REAL cohort study findings [7] and CQC report [9, 35], we estimate 160 NHS and 80 independent sector patient participants will be discharged during the 12 month recruitment period in C1 (without readmission) and around 33% NHS patients will be readmitted during follow-up. Thus, for our main secondary outcome, this sample size (240 patients) will allow us to detect a difference in readmission of 22.3% between NHS and independent sector units with 90% power or 19.7% with 80% power (based on a Z-test comparing two proportions) and 5% significance level assuming the same VIF and DE as above.

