**Methods:**

ACER comprises a:1) detailed survey of NHS and independent sector inpatient mental health rehabilitation services across England; 2) qualitative investigation of patient, family, staff and commissioners’ experiences of the two sectors; 3) cohort study comparing clinical outcomes in the two sectors over 18 months; 4) comprehensive national comparison of inpatient service use in the two sectors, using instrumental variable analysis of routinely collected healthcare data over 18 months; 5) health economic evaluation of the relative cost-effectiveness of the two sectors. In Components 3 and 4, our primary outcome is ‘successful rehabilitation’ defined as a) being discharged from the inpatient rehabilitation unit without readmission and b) inpatient service use over the 18 months.

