#### Procedure and data collection

We will follow participants recruited in C1 for 18 months and compare total inpatient days from recruitment, including any readmissions, for those in NHS and independent sector units. To account for the fact that independent sector patients are likely to have less time to relapse (due to longer admissions) than those in NHS units, our main analysis will compare readmissions for those discharged during the 12-month recruitment period in C1. However, we will also conduct a supportive analysis including all patients discharged during the 18-month follow-up period.

We have successfully tracked similar patient cohorts and will gain participants’ consent for this at recruitment in C1. We plan to follow their progress through contact with key staff and will record contact details for these staff at recruitment into C1 (including the participant’s local CCG and NHS Trust and their community care co-ordinator or care manager). We will contact the manager of inpatient rehabilitation units that participated in C1 every month to confirm whether any patient participants have been discharged or transferred to another inpatient unit. Where this is the case, we will record the date of transfer/discharge and details of where the patient has moved to and confirm contact details for key staff involved in their ongoing care such as their community care co-ordinator. This staff member will be the patient participant’s ‘key staff contact’ for the remainder of the study and we will continue to keep in contact with them monthly to track the patient’s progress and the dates of any further admissions. We will collect from the key staff contact at six, 12 and 18 months details following discharge about the patient’s use of mental health supported accommodation (residential care, 24 h supported housing, < 24 h supported housing), the number of hours and cost per week of any additional ‘care packages’ funded by the NHS or social services that are in place to support them in the community and the length of time any such care packages have been in place, any readmissions (including general medical admissions), number of visits to Accident and Emergency, and the number of community contacts.

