### Component 5: Health economic evaluation calculating the relative cost effectiveness of inpatient rehabilitation services provided by the NHS and the independent sector 

Component 5 (C5) will address research question 5:

5.Is inpatient rehabilitation more cost effective when provided by the independent sector or the NHS, after adjusting for differences between the sectors in terms of key predictors of costs such as patient characteristics and length of stay?

The main cost-utility analysis (CUA) will use information from C1 and C3 to calculate the incremental cost per quality-adjusted life-year (QALY) gained by using independent sector rehabilitation services compared to NHS rehabilitation services, over the 18-month period. The largest costs are expected to be due to inpatient rehabilitation days (i.e. the primary statistical outcome), but the cost perspective will also include other NHS and Personal Social Services resource use to describe the wider support provided to participants.

The supporting cost-effectiveness analysis will calculate the incremental cost per readmission avoided (this is the secondary statistical outcome) for those discharged during the 12-month recruitment period in C1/C3. We will also conduct a supportive analysis including all patients discharged during the 18-month follow-up period of C1/C3.

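### The readmission power statement counts patients discharged without readmission, whereas the planned analysis takes everyone discharged in the 12-month period

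*Protocol article*

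**What the plan says.** The Component 3 section on procedure and data collection fixes the set for the readmission comparison: "our main analysis will compare readmissions for those discharged during the 12-month recruitment period in C1". It adds that "we will also conduct a supportive analysis including all patients discharged during the 18-month follow-up period". Neither sentence puts a condition on later readmission. Component 5 uses the same set for cost per readmission avoided, "for those discharged during the 12-month recruitment period in C1/C3".

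The Component 3 sample size section describes the patients behind the power statement differently. It expects 160 NHS and "80 independent sector patient participants will be discharged during the 12 month recruitment period in C1 (without readmission"), and in the same sentence that "around 33% NHS patients will be readmitted during follow-up". From these 240 it concludes that the study can "detect a difference in readmission of 22.3% between NHS and independent sector units with 90% power or 19.7% with 80% power". The method named for this is a two-sample comparison of proportions, with the inflation factors already used for the primary outcome.

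The abstract uses almost the same phrase, "being discharged from the inpatient rehabilitation unit without readmission", as part of its definition of successful rehabilitation. The Component 3 analysis section names logistic regression on the proportion readmitted and does not restate the denominator.

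**The concern.** One endpoint has two descriptions of its denominator. The procedure section and Component 5 count everyone discharged in the window. The sample size section counts those discharged without readmission, which in the abstract's terms is close to a count of successes, and uses it as the set in which readmissions are to occur. The text does not say over what period the qualifier applies. A reader therefore cannot tell whether 160 and 80 are the expected size of the analysed set or a subset of it.

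Two things are at stake. The detectable difference rests on a count that may not belong to the analysis. In addition, someone drafting the detailed analysis could take the narrower description as the denominator. That would choose patients on the outcome and remove early readmissions. It would tend to remove more of them from the NHS arm, since the procedure section itself expects independent sector patients to stay longer and have less time to relapse.

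**Working it through.** **Inputs.** All come from the Component 3 sample size section: 160 NHS and 80 independent sector patients, NHS readmission 33%, VIF 1.19, DE 1.42, Z-test of two proportions at 5% (two-sided assumed).

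**Formula.** Power = Φ[(|p1 − p2| − 1.96·s0)/s1], with s0 = √[p̄(1 − p̄)(1/n1 + 1/n2)], s1 = √[p1(1 − p1)/n1 + p2(1 − p2)/n2] and p̄ the weighted mean of p1 and p2. The n are effective numbers, after division by 1.19 × 1.42 = 1.69.

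**1. Reproducing the stated figures.** 240/1.69 = 142, or 71 per arm if split equally.
- 33% v 10.7%: s0 = 0.0694, s1 = 0.0668; (0.223 − 0.136)/0.0668 = 1.30; power 90%.
- 33% v 13.3%: s0 = 0.0708, s1 = 0.0688; (0.197 − 0.139)/0.0688 = 0.85; power 80%.

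Both stated differences are matched. So the full 240, described as discharged without readmission, was entered as the number at risk of readmission, and as equal halves.

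**2. If 160 and 80 are in fact all dischargees.** Effective n = 94.7 and 47.3.
- 22.3 points: s0 = 0.0776, s1 = 0.0660; (0.223 − 0.152)/0.0660 = 1.07; power 86%.
- 19.7 points: s0 = 0.0785, s1 = 0.0691; (0.197 − 0.154)/0.0691 = 0.62; power 73%.

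Solving for the difference gives 23.4 points at 90% power and 21.0 at 80%.

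**3. If 160 and 80 leave out patients already readmitted.** Let r be the share of dischargees left out, assumed equal in both sectors. The set in the procedure section is then 160/(1 − r) and 80/(1 − r).

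| r (assumed) | NHS / independent | 90% power | 80% power |
|---|---|---|---|
| 0 | 160 / 80 | 23.4 | 21.0 |
| 10% | 178 / 89 | 22.4 | 20.1 |
| 20% | 200 / 100 | 21.4 | 19.1 |
| 33% (never readmitted) | 239 / 119 | 19.8 | 17.6 |

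The last row is hard to credit: 160/0.67 = 239 of a target of 250 NHS patients would have to be discharged within the period.

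**4. What would be lost if the narrower set were analysed.** The protocol gives no timing for discharges or readmissions, so this step rests on assumption: a constant readmission hazard set to give 33% overall. If a share s of readmissions falls inside the window and those patients are dropped, the NHS rate in the rest is 0.33(1 − s)/(1 − 0.33s).

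| Assumed timing | s | NHS rate left |
|---|---|---|
| Calendar window, staggered entry | 23% | 27.5% |
| Own clock, discharge in months 6–12 | 37% | 23.7% |
| Own clock, discharge spread over months 0–12 | 54% | 18.5% |
| Own clock, discharge in months 0–6 | 65% | 14.7% |

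The loss is roughly a quarter to two-thirds of readmissions, and the assumed timing decides where in that range it falls.

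**The case against.** The strongest reply is that the analysis set is not in doubt. The procedure section fixes it, Component 5 repeats it, and a planning sentence does not specify an analysis. This stands. A reader might infer that the study will discard about half its readmissions, but the document plans no such exclusion. The figure of about half also needs each patient's own 12-month clock with discharges spread evenly across it. The protocol speaks of a recruitment period, which reads more naturally as a calendar window and puts the loss in the lower part of the range.

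Second, the qualifier has a coherent meaning: not readmitted within the 12-month period, with about 33% readmitted afterwards. This also stands, since the protocol does not say which patients the 33% is based on. So a reader should not conclude that the power statement is impossible, for instance because a 22.3-point fall from a depleted NHS rate would go below zero. That holds only under some timing assumptions and only for a reduction. Even on the coherent reading, however, the set is selected on the outcome and is not the one in the procedure section.

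Third, if patients already readmitted were left out, the real set is larger, so the wording taken alone makes the power statement conservative. This is correct, and it limits the point to a correction of the planning figure.

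**Conclusion.** The inconsistency is on the page. The power statement is built on patients discharged without readmission, while the analysis is defined on all patients discharged in the 12-month period. The documents do not show that 160 and 80 are the size of the analysed set.

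At the actual 2:1 split, the 90%-power difference lies between about 23.4 points (160 and 80 are all dischargees) and 21.4 points (20% of dischargees left out), against 22.3 stated. The 80%-power difference lies between 21.0 and 19.1, against 19.7 stated. These figures assume a pooled two-sided Z-test, a lower rate in the independent sector, the protocol's VIF and DE, and an equal share left out in both sectors.

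The concern is limited to the definition of the set and the count behind one stated figure. The documents do not support a claim that the planned analysis is biased.

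**What to change.** Delete the parenthetical no-readmission qualifier from the Component 3 sample size section. State one at-risk set in the Component 3 procedure, sample size and analysis sections and in Component 5: all participants discharged to the community in the 12-month period, with any readmission after that discharge counted as an event.

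Confirm from the source figures whether 160 and 80 count all dischargees, and re-derive them if they do not. Then restate the detectable difference from those counts and their actual split, with the 33% NHS rate, VIF 1.19 and DE 1.42.

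The cost is a few words and a rerun of one sample size line, with no new data or patients. The drawback is that the published figure may become slightly more or less favourable.

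### The detectable readmission differences of 22.3 and 19.7 points do not follow from the stated 160:80 split, and they carry no direction although they hold only if independent-sector readmission is lower

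*Protocol article*

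**What the plan says.** The relevant text is the last paragraph of the protocol article's Component 3 section, Sample size estimation. It gives the expected numbers: "we estimate 160 NHS and 80 independent sector patient participants will be discharged during the 12 month recruitment period in C1". It sets the reference rate: "around 33% NHS patients will be readmitted during follow-up". From these 240 patients it claims power to "detect a difference in readmission of 22.3% between NHS and independent sector units with 90% power or 19.7% with 80% power". The method is given as "based on a Z-test comparing two proportions) and 5% significance level assuming the same VIF and DE as above". The two inflation factors come from the preceding paragraph: "using a variance inflation factor (VIF) of 1.19" and "a design effect (DE) of 1.42 (based on an average cluster size of 8 and an intracluster correlation of 0.06".

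The paragraph does not say that the 240 are treated as two equal groups. It does not say whether the Z-test uses pooled or unpooled variance, and it does not say whether the difference is an increase or a decrease from 33%. Research question 4 (Aim and research questions, and again at the head of Component 3) asks which of the two sectors is the more effective at preventing readmission, so either direction is of interest.

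**The concern.** Two things look wrong. First, the text predicts a 2:1 split, yet the printed differences look like those of a 1:1 split, which is more efficient for the same total. Second, a detectable difference measured from a fixed 33% is not symmetric. A fall moves the independent-sector rate towards 11–13%, where the binomial variance is small. A rise moves it to 53–55%, where the variance is near its maximum. A single undirected figure therefore cannot describe both cases.

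Readmission is the outcome named in research question 4, and it is the effect measure in the supporting cost-effectiveness analysis of Component 5. A reader would take 90% power at 22.3 points to apply whichever sector does worse, and might then take a null result as stronger evidence against excess independent-sector readmission than the numbers allow.

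**Working it through.** **Inputs** (all from Component 3, Sample size estimation): n = 160 NHS and 80 independent; NHS proportion p₁ = 0.33; VIF 1.19; design effect 1.42; 5% significance. Sidedness is not stated; two-sided is assumed (z = 1.96).

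**Effective numbers.** 1.19 × 1.42 = 1.6898. Then n₁ = 160/1.6898 = 94.7 and n₂ = 80/1.6898 = 47.3. For an equal split, 120/1.6898 = 71.0 per group.

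**Formulas.** With d = |p₁ − p₂|:
- S₁ = √[p₁(1−p₁)/n₁ + p₂(1−p₂)/n₂]
- S₀ = √[p̄(1−p̄)(1/n₁ + 1/n₂)], where p̄ is the weighted mean of p₁ and p₂
- Pooled power = Φ[(d − 1.96·S₀)/S₁]
- Unpooled power = Φ[d/S₁ − 1.96]

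**Step 1: can the printed pair be reproduced?** With 71.0 v 71.0 and lower independent-sector readmission, pooled:
- d = 0.223, p₂ = 0.107: S₀ = 0.0693, S₁ = 0.0668; (0.223 − 0.1359)/0.0668 = 1.304; power 90.4%.
- d = 0.197, p₂ = 0.133: S₀ = 0.0708, S₁ = 0.0688; (0.197 − 0.1387)/0.0688 = 0.846; power 80.1%.

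Solved for d, this gives 22.2 and 19.7 points. In reverse, each printed difference needs 71 per group, and 142 × 1.19 × 1.42 = 240. So the printed pair matches an equal split to rounding.

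**Step 2: the stated 160:80 split, decrease, pooled.**
- d = 0.223: p̄ = 0.2557, S₀ = 0.0776, S₁ = 0.0660; (0.223 − 0.1522)/0.0660 = 1.073; power 85.8%.
- d = 0.197: p̄ = 0.2643, S₀ = 0.0785, S₁ = 0.0691; (0.197 − 0.1538)/0.0691 = 0.625; power 73.4%.

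**Step 3: the same split, increase, pooled.**
- d = 0.223, p₂ = 0.553: S₀ = 0.0874, S₁ = 0.0869; (0.223 − 0.1712)/0.0869 = 0.596; power 72.4%.
- d = 0.197, p₂ = 0.527: S₀ = 0.0870, S₁ = 0.0872; (0.197 − 0.1706)/0.0872 = 0.303; power 61.9%.

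**Step 4: summary** (stated VIF and design effect; first figure for 90% power or 22.3 points, second for 80% power or 19.7 points).

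| Split, variance | Direction | Detectable (points) | Power at 22.3 / 19.7 |
|---|---|---|---|
| 160:80 pooled | lower | 23.4 / 21.0 | 86% / 73% |
| 160:80 unpooled | lower | 21.7 / 19.4 | 92% / 81% |
| 160:80 pooled | higher | 28.2 / 24.5 | 72% / 62% |
| 160:80 unpooled | higher | 27.8 / 24.3 | 73% / 62% |
| 120:120 pooled | lower | 22.2 / 19.7 | 90% / 80% |
| 120:120 pooled | higher | 26.7 / 23.2 | 77% / 66% |

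Two other standard variants at 160:80 for a decrease, arcsine (22.9 / 20.4) and simple-average pooling (22.8 / 20.4), do not give the printed pair either.

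**Step 5: sensitivity to the design effect.** The factor 1.42 assumes 8 patients per unit, but the readmission analysis uses only discharged patients. If 497 patients at 8 per unit means about 62 units, 240 discharged patients are about 3.8 per unit, and the design effect is 1 + 2.8 × 0.06 ≈ 1.17. Pooled at 160:80, this gives 21.6 / 19.3 points lower (power at the printed differences 92% / 82%) and 25.7 / 22.2 points higher (80% / 70%). The unit count is inferred; the protocol does not state one.

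**The case against.** The strongest reply is that the protocol does not specify pooled variance. For a decrease, the printed figures lie between the pooled and unpooled answers. Under the unpooled formula they are slightly conservative, and under a design effect suited to the discharged subset they are conservative even when pooled. The planned analysis is a clustered, adjusted logistic regression, so the Z-test is only a planning approximation, and the protocol admits that the VIF is an assumption without prior estimates. All of this stands. A reader might infer from the 160:80 recalculation that the promised power is simply not delivered. For a decrease the document does not support that, because the answer turns on a formula it leaves open.

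It can also be said that quoting one direction is common, and that the introduction to Component 3 raises fewer independent-sector readmissions as the scenario that would justify longer stays. That makes a decrease a reasonable planning direction. It does not make the undirected sentence correct: the figures are not limited to that direction, the research question asks about either sector, and neither variance formula restores the stated power for an increase.

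Finally, a reader might treat the equal split as established. It is an inference from the close numerical match; the protocol never states it.

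**Conclusion.** The point holds, with moderate weight. The printed 22.3 and 19.7 points do not follow from 160 v 80 under any of the standard two-sided formulas tried with the stated VIF and design effect. They agree, to rounding, with 120 v 120 and lower independent-sector readmission. For a decrease the gap is 1.1 to 1.3 points if variance is pooled, and the printed figures are slightly conservative if it is not.

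The larger problem is direction. If independent-sector readmission is higher, about 28 and 24 points are needed, and the printed differences have about 72% and 62% power, almost regardless of the variance formula. These results assume a two-sided 5% test and an NHS rate of 33%.

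A reader might conclude that the study is undersized or that the sentence must be corrected before the study can proceed. Neither follows. The target of 500 is driven by inpatient days, and that chain reproduces: a normal approximation gives 292 against the stated 294, then 294 × 1.19 = 350 and 350 × 1.42 = 497. The sentence concerns a secondary outcome, and no population, analysis or recruitment target depends on it.

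**What to change.** Restate the sentence for the 160:80 split, name the variance formula and the sidedness, and give both directions. With pooled variance, two-sided 5%, VIF 1.19 and design effect 1.42, the detectable differences from 33% are 23.4 points (90% power) or 21.0 points (80%) if independent-sector readmission is lower, and 28.2 or 24.5 points if it is higher.

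Optionally, add a sensitivity figure with a design effect for the discharged subset, with its assumption stated (about 3.8 patients per unit over about 62 units, design effect about 1.17): 21.6 / 19.3 points lower and 25.7 / 22.2 points higher.

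The cost is one rewritten sentence. With the stated design effect and pooled variance the figures become less favourable, slightly for a decrease and more clearly for an increase. Recruitment, the primary-outcome calculation and the planned analyses stay as they are.

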#### Analysis

We will conduct two statistical analyses using the information collected from C1 and C3:

i.Multivariable regression

We will conduct linear regression using total inpatient days (since recruitment to C1) as our primary outcome and logistic regression using proportion of patients readmitted as our main secondary outcome, allowing for clustering within inpatient rehabilitation units. Service sector (independent or NHS) will be included in the model as the main explanatory variable. We shall adjust for relevant sociodemographic and clinical confounding variables, including inpatient days up to recruitment (gathered in C1), which may account for differences in outcomes between the two service types. We will use Directed Acyclic Graphs (DAGs) to ensure a logical and consistent approach to identifying potential confounders [36]. Suitable transformations will be used if assumptions of normality for linear regression are not satisfied. In addition, we will conduct exploratory analysis to investigate the relationship between the length of the inpatient rehabilitation admission (i.e. ‘dose’ of rehabilitation assessed in inpatient days), readmission and the service sector (independent or NHS), through a mediation analysis. Bias due to missing data in the explanatory variables (gathered in C1) will be investigated and we will use multiple imputation based on chained equations to impute missing values for these variables as appropriate.

ii.Multivariable regression with propensity score

In this two-stage approach, an initial regression generates a propensity score, the probability of ‘exposure’ (admission to an independent sector unit) conditional on sociodemographic and clinical covariables identified in C1. The propensity score is then included in a second appropriate regression, accounting for clustering, in which the main outcome variable is successful rehabilitation at 18 months (defined as before). This approach allows us to account for the principal confounders influencing why (e.g. the patient’s health state) a person is admitted to an independent sector unit rather than an NHS unit (i.e. confounding by indication). A major issue when estimating propensity scores is the presence of missing values in the explanatory variables. Multiple imputation will be used to handle missing data under missing at random (MAR) assumption, and the two-stage analysis will be performed in each imputed dataset. The results are then combined using Rubin’s rule to obtain an overall estimate of the effect of service sector on successful rehabilitation. We will also conduct sensitivity analyses following the methods recommended by Blake et al. [37] if the MAR assumption is not considered plausible.

